## Abstract

Typhoid fever remains a significant health problem in sub-Saharan Africa, with incidence rates of >100 cases per 100,000 person-years of observation. Despite the prequalification of safe and effective typhoid conjugate vaccines (TCV), some uncertainties remain around future demand. Real-life effectiveness data, which inform public health programs on the impact of TCVs in reducing typhoid-related mortality and morbidity, from an African setting may help encourage the introduction of TCVs in high-burden settings. Here, we describe a cluster-randomized trial to investigate population-level protection of TYPBAR-TCV^®^, a Vi-polysaccharide conjugated to a tetanus-toxoid protein carrier (Vi-TT) against blood-culture-confirmed typhoid fever, and the synthesis of health economic evidence to inform policy decisions. A total of 80 geographically distinct clusters are delineated within the Agogo district of the Asante Akim region in Ghana. Clusters are randomized to the intervention arm receiving Vi-TT or a control arm receiving the meningococcal A conjugate vaccine. The primary study endpoint is the total protection of Vi-TT against blood-culture-confirmed typhoid fever. Total, direct, and indirect protection are measured as secondary outcomes. Blood-culture-based enhanced surveillance enables the estimation of incidence rates in the intervention and control clusters. Evaluation of the real-world impact of TCVs and evidence synthesis improve the uptake of prequalified/licensed safe and effective typhoid vaccines in public health programs of high burden settings. This trial is registered at the Pan African Clinical Trial Registry, accessible at Pan African Clinical Trials Registry (ID: PACTR202011804563392).

## 1. Introduction

Typhoid fever (TF), caused by the *Salmonella enterica* subspecies *enterica* serovar Typhi (*S.* Typhi), is one of the most common causes of bacteremia in several low- and middle-income countries and caused an estimated 10.9 million cases and 116,000 deaths globally in 2017 [1]. Whilst TF can affect all age groups, the incidence is higher in preschool and school-age children compared to older people [2]. TF incidence estimates suggest that south-central Asia, Southeast Asia, and southern Africa are regions with high incidence, defined as >100 cases per 100,000 person years, particularly in subregions with limited access to improved water quality and with poor access to sanitation [1,3,4,5]. Recent data from the Typhoid Surveillance in Africa Program revealed marked heterogeneity in the incidence of TF in different surveillance sites across the African continent, with some areas having rates of >100 per 100,000, including Ghana, Burkina Faso, and Madagascar [1,6,7].

Most typhoid cases are effectively treated with antibiotics, although the case fatality rate remains at about 1% [1]. Moreover, growing rates of antibiotic resistance and extensively drug-resistant *S*. Typhi strains, resistant to first-line antimicrobials chloramphenicol, ampicillin, and trimethoprim-sulfamethoxazole; fluoroquinolones; and third generation cephalosporins, in many countries reduce the number of viable treatment options and necessitate increasingly complicated and costly alternatives [8]. Improvements in water quality, sanitation infrastructure, and implementation of hygienic practices can reduce TF disease burden as has been observed in high-income countries [9]. However, the development of adequate infrastructure for improved water and sanitation requires large and long-term investments and is therefore a distant reality for impoverished populations. Instead, limited economic opportunities in rural settings have led to rapid resource-poor urbanization and unsustainable population density, significantly contributing to the risk of typhoid transmission [10]. Additionally, basic health education for handwashing and proper food handling has had measured effects in reducing TF [11], which would take time to implement in the community.

In October 2017, the WHO has recommended the use of TCV in typhoid-endemic countries from the age of 6 months onwards, administered as a single dose and programmatic administration in combination with other childhood vaccines at 9 months of age or in the second year of life [12]. A position paper has since been published in 2018 updating recommendations on typhoid vaccination, superseding a position paper from 2008 [12]. Where feasible and supported by epidemiologic data, catch-up vaccination in children and adolescents up to 15 years of age is also recommended. The position paper highlights that the introduction of TCVs should be prioritized in countries with a high burden of TF or a high prevalence of antimicrobial resistance. Several areas for further research were highlighted, particularly better understanding the duration of protection afforded by a single dose, the need for re-vaccination, and the need to identify immunological correlates of protection. TYPBAR-TCV^®^, a Vi-polysaccharide conjugated to a tetanus-toxoid protein carrier (Vi-TT), was prequalified by the WHO in January 2018 and Gavi the Vaccine Alliance has committed an $85 million funding window to support the roll out of TCV in eligible countries between 2019 and 2020.

Overall, TCVs have been shown to have a reassuringly safety profile across age groups including infants and children [13,14,15,16,17]. An individually randomized trial of Vi-TT in Nepal, conducted by the Typhoid Vaccine Acceleration Consortium (TyVAC) led by the University of Maryland in partnership with the University of Oxford and PATH, determined the vaccine efficacy to be 81.6% (95% confidence interval, between 58.8% and 91.8%), while another trial in Malawi is expected to provide estimates of efficacy within this year [18,19]. Furthermore, a cluster-randomized TyVAC trial in Dhaka, Bangladesh, will provide an estimate of the population level Vi-TT effectiveness [20].

As of January 2021, Vi-TT is licensed for use in nine countries worldwide including Tanzania, Ghana, Kenya, and Zambia. However, large-scale effectiveness data of TCVs in many African settings are still limited. Effectiveness data provide critical input to decision making by national and regional stakeholders to drive country and regional uptake in Africa, where the epidemiology of typhoid fever differs from South Asia. Nonetheless, there are no cluster-randomized trials currently ongoing on the continent and population-level protection data are largely lacking. Herein, we present the design of the first cluster-randomized trial assessing the real-world vaccine effectiveness of TCVs in preventing typhoid fever on the African continent. The data generated will be used in estimating the budgetary impact and in understanding the value of the money invested in the potential introduction of TCV in Ghana.

## 2. Materials and Methods

### 2.1. Trial Design

The Typhoid Conjugate Vaccine Effectiveness in Ghana (TyVEGHA) study is a participant- and observer-blinded, cluster-randomized phase IV trial with clusters randomized to receive Vi-TT or the control vaccine MenAfriVac (group A meningococcal polysaccharide–tetanus toxoid conjugate vaccine (MCV-A)) to evaluate the effectiveness and safety of Vi-TT in Ghanaian children and adolescents. The cluster-randomized design was selected in order to assess both the individual-level effectiveness (on vaccinees) and population-level effectiveness (on both vaccinees and non-vaccinees) including herd protection of vaccination of children and adolescents aged 9 months to <16 years living in the Asante Akim District in Ghana for a period of 3 years. The first vaccination was conducted through a cluster level mass vaccination of age eligible children (Year 1), followed by annual catch-up vaccinations (Year 2 and 3) for age-eligible children and adolescents at the trial sites. Enhanced passive surveillance was conducted in parallel in the trial catchment area to identify blood-culture-confirmed TF cases.

This trial is registered at the Pan African Clinical Trial Registry, accessible at www.pactr.org (ID: PACTR202011804563392).

### 2.2. Cluster Randomization and Method of Blinding

The TyVEGHA study population was recruited from a geographically defined catchment area in the Asante Akim District of Ghana (see Figure 1, TyVEGHA catchment area). The baseline map of the area was developed in partnership with the Statistical Service office in Agogo, Ghana. Additional data from a baseline census were used to inform details on the map and to confirm the catchment area boundaries for the trial. The census population data were merged with the Geographic Information System mapping (GIS,) data for cluster formation (QGIS.org, 2021. QGIS Geographic Information System. QGIS Association.). The study area was divided into 80 clusters. Each cluster consisted of a total population of 400–600 inhabitants at average, with an estimated proportion of 40% in the eligible age group for TyVEGHA. The entire age-eligible cluster population was eligible for vaccination and analized under primary analysis. In addition, a buffer region formed at the border of each cluster, was drawn to insulate adjacent clusters, minimizing cross-cluster transmission [21] if necessary. The age-eligible individuals residing in the inner region served as the population under exploratory analysis.

GIS mapping tools were used for identification of all geographical characteristics and demarcation of clusters [22]. Randomization lists allocated each cluster to receive either Vi-TT or the control vaccine MCV-A in equal numbers (40 clusters in each arm), based on population size, using stratified block randomization. Stratification was by clusters, the distance to the closest healthcare facility (above the median versus at or below the median), and the percentage of children and adolescents aged 9 months to <16 years age (above the median versus at or below the median).

Once participants will be enrolled in the study, they will be vaccinated with either the trial or the control vaccine according to the residential cluster in which they live. Census updates were conducted annually to identify birth and mortality rates as well as in- and out-migration in the defined clusters. The census was designed to capture (1) socioeconomic information of the households, including profession, household income, and level of education and (2) healthcare-seeking behavior and to access to water, sanitation, and hygiene (WaSH) infrastructure. Household verbal consent for the census was provided by the head or a key informant of the household.

### 2.3. Study Participants

A total of 23,000 eligible children and adolescents will be vaccinated—11,500 each in the Vi-TT and MCV-A arms. A subset for immunogenicity assessment will include 600 children and adolescents aged 9 months to <16 years (1:1 ratio by age strata; <5 years and ≥5 years, individually randomized 2:1 ratio by intervention and comparator), and a subset for safety monitoring will include 3000 children and adolescents aged 9 months to <16 years (individually-randomized, 1:1 ratio by intervention and comparator) (see Figure 2, trial flowchart).

To be eligible to participate in the study, the individual will be healthy, aged 9 months to <16 years (i.e., ≤15 years and 364 days) at the time of vaccination, voluntarily provide consent via their parents or legally authorized representative (LAR), and live within the study cluster at the time of vaccination.

Individuals will not be enrolled if they, or a parent or LAR, report a history of allergic reactions to any vaccine component, ongoing acute and/or chronic illness, or any coagulopathies (e.g., bleeding tendencies); if there are any compelling medical or social reasons in the judgment of a physician; if they are pregnant (including self- or parent-/LAR-reported or positive urine testing) or are lactating; or if they received a typhoid vaccination (proven by presentation of a vaccine card or parent-/LAR-reported) in the last 5 years prior to presentation.

Participants will be temporarily excluded if, at the time point of vaccination, the parent/LAR reported fever (elevated tympanic (≥38 °C) or axillary temperature (≥37.5 °C)) in the child within 24 h and/or the use of antipyretics within 4 h prior to vaccination or if they received any other vaccination during the previous 4 weeks (confirmed by vaccine card or parent-/LAR-reporting). Females ≥11 years of age with self- or parent-/LAR-reported irregular menstruation or who did not know their last menstruation date will be reassessed and consented at or after their next menstrual period. A reassessment at least 48 h after the initial screening of resolving the condition of temporary exclusion criteria will be conducted to ensure these temporary exclusion criteria no longer existed.

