### 2.4. Vaccination and Immunogenicity Assessment

The trial staff identified potential participants living in the 80 clusters of Asante Akim North, Ghana. Trial staff, including community health volunteers, will systematically approach each household in the area to identify households with children and adolescents that will be age-eligible at the time of vaccination. Once a household with a potential participant will be identified, the parent/LAR of the child will be given basic information about the trial and invited to attend the nearest study vaccination clinic.

After arrival at the study clinic, participants and their parents/LAR will be provided with an explanation of study objectives and invited to participate following written informed consent. Assent will be sought for participants ≥11 years of age. Once consent and assent (as appropriate) will be obtained, trial staff will screen volunteers according to the inclusion/exclusion criteria and conduct a medical examination, including measuring baseline temperature to assess for temporary exclusion criteria. Demographic information (including age and address) and participant/parent/LAR contact details will be updated during this visit. Participants or their parent/LAR meeting at least one temporary exclusion criteria after the medical assessment will be informed of the reason and asked to return in ≥48 h after resolving the condition of temporary exclusion criteria for repeat assessment and re-consenting.

Consented participants will be randomized by cluster to receive either Vi-TT or MCV-A. The randomization list by cluster will be computer-generated prior to the start of the vaccination campaign and will be provided to the staff assigned for randomization to reduce discriminatory practices or unfair assignment of vaccines. Based on the cluster randomization, the appropriate vaccine will be administered by a trained member of the study team. The site of vaccination will be recorded. If the participant’s parent/LAR consent to participation in the immunogenicity substudy, a blood sample will be collected prior to vaccination by a trained staff member. The participant will be considered enrolled in the study at the point in that any medical procedure took place (i.e., blood sample collected or vaccination administered).

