A study card will be provided during the annual update census, which contains the name of the study, the participant ID, and contact details for the study team will be given to all participants/parents/LAR for use if they have any concerns or if their child is admitted to hospital at any time during the study. The study card will also contain instructions for attending the study health care facilities or sentinel sites if the participant develops a fever at any time over the follow-up period of three years.

A subset of 600 participants will be selected on a 2:1 ratio (Vi-TT vs. MCV-A) to have blood samples collected at baseline (Day (D) 0) and at D28, D365, D730 and D1095 post-vaccination to assess vaccine immunogenicity. Safety assessments will include an active safety follow-up contact on day 7 to monitor adverse events following immunization in participants in the safety substudy (*n* = 3000, 1:1 assignment to intervention and control group) using study diary cards, and 3 years of passive hospital-level febrile and severe adverse event (SAE) surveillance. An independent Safety Monitoring Committee (SMC) was established to assess safety results and to correspond with the Data Safety Monitoring Board (DSMB). Randomization lists for these subsets will be generated prior to the vaccination campaign by an independent statistician who is not part of the study. The selection of these participants were age-stratified (<5 years vs ≥5 years of age, with an allocation ratio of 1:1) (Figure 1). Participants who will be enrolled in the immunogenicity substudy will receive additional face-to-face follow-up visits at the Agogo healthcare facility. At these additional visits, blood samples will be collected along with information relating to fever episodes or SAEs since the previous contact.

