### 2.6. Sample Size/Statistical Methods

The sample size was calculated by assuming an expected cumulative incidence rate of typhoid fever in control clusters over 3 years of 36 cases per 10,000 person-years in a catchment population of 21,213 i.e., 45,961.5 person-years of risk. Based on a preliminary analysis of survey data from the target population, we assumed that 50% of febrile illness cases seek healthcare at Agogo Presbyterian Hospital [24]. A total of 80 clusters were formed in 15 villages considering the natural settlement of the population and administrative borders. The current average number of children and adolescents aged 9 months to less than 16 years per village was 287 based on the population census in 2019 (see Table 1). We estimated the vaccine coverage at 65% and a total effectiveness of 80% with a coefficient of variation of 0.5 for a one-sided test of significance at an alpha of 0.05.

Following Hayes and Moulton, a total sample size of 13,200 person-years, which was obtained by sampling 80 clusters (40 in each arm) with an average cluster size ranging from 145 to 180, achieved >80% power to detect a total effectiveness of 80% between the intervention event rate 0.0007 and the control event rate 0.0036 [25]. The between-cluster coefficient of variation in the control and treatment groups was assumed as 0.500. A two-sided t-test of the event-rate difference was used with a significance level of 5%. The total sample sizes ranging from 11,600 to 14,400 adjusted for 15% drop-out rate were within target eligible population size considering 65% vaccine coverage.

For the immunogenicity substudy, a total of 600 children and adolescents will be enrolled, stratified by age (<5 years and ≥5 years). Each age stratum was randomized 2:1 to receive the intervention (*n* = 200) or control vaccine (*n* = 100) with an assumption of a 90% reference seroconversion rate, −10% of non-inferiority margin, and 25% drop-out rate.

For the safety monitoring substudy, a total of 3000 children and adolescents with a 1:1 ratio of each arm will be enrolled according to the “rule of three” to detect at least one event with 1500 participants in each arm. The upper limit of 95% CI of the incidence rate yielded 0.2% in each arm [26].

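### The safety and immunogenicity subsets are described as individually randomized to vaccine, although the vaccine is fixed by cluster of residence

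*Protocol article*

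**What the plan says.** Two rules for who gets which vaccine stand side by side in the protocol article.

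**Vaccine by cluster.** Section 2.2 has enrolled participants "vaccinated with either the trial or the control vaccine according to the residential cluster in which they live". Section 2.4 repeats it: "Consented participants will be randomized by cluster to receive either Vi-TT or MCV-A", and then "Based on the cluster randomization, the appropriate vaccine will be administered by a trained member of the study team". The same paragraph of Section 2.4 goes on to the pre-vaccination blood sample for immunogenicity participants and makes no exception for them.

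**Vaccine by individual.** Section 2.3 calls the immunogenicity subset (600) "individually randomized 2:1 ratio by intervention and comparator" and the safety subset (3,000) "individually-randomized, 1:1 ratio by intervention and comparator". Section 2.6 says of the immunogenicity subset: "Each age stratum was randomized 2:1 to receive the intervention" (200) or the control vaccine (100).

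**Text between the two.** Section 2.4 also says "A subset of 600 participants will be selected on a 2:1 ratio (Vi-TT vs. MCV-A) to have blood samples collected" and calls the step a selection. Yet it speaks of randomization lists for the subsets, prepared before the campaign, and of a 1:1 assignment for the safety subset.

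On safety precision, Section 2.6 applies the rule of three to 1,500 per arm: "The upper limit of 95% CI of the incidence rate yielded 0.2% in each arm".

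**The concern.** In a cluster-randomized trial the unit of allocation must be unambiguous. Being randomized in a 2:1 ratio to receive a vaccine describes treatment allocation, not sampling. Staff would hold a cluster list and separate subset lists, and the article does not say that the subset lists decide only who is bled or followed actively.

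Two things are at stake. If a subset list were taken to decide the vaccine, some children in control clusters would get Vi-TT and some in Vi-TT clusters would get MCV-A. That would dilute the primary comparison and blur the overall and indirect comparisons. If the vaccine follows the cluster, no child's vaccine is individually randomized, and a reader of Section 2.3 would wrongly take the safety and immunogenicity contrasts as individually randomized evidence on independent participants.

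**Working it through.** **Inputs.** From Section 2.3: 11,500 vaccinees per arm, and subsets of 600 (2:1) and 3,000 (1:1). From Section 2.2: 40 clusters per arm. From Section 2.6: event rates 0.0036 and 0.0007, effectiveness 80%, coverage 65%, between-cluster coefficient of variation k = 0.5 (primary endpoint), 1,500 per arm for safety, 25% drop-out for immunogenicity. Assumptions added here: the subsets do not overlap, half of each comes from each arm's clusters, subset children are spread evenly over clusters, and herd effects are ignored.

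**1. The plan's own figures.** Rule of three: 3/1,500 = 0.200%. Exact: 1 − 0.05^(1/1,500) = 0.1995%. The stated 0.2% reproduces, for independent participants.

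Primary power by the Hayes–Moulton formula, c = 40 clusters per arm, y = 165 person-years per cluster, two-sided 5%:

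power = Φ{√[(c − 1)(λ0 − λ1)² / ((λ0 + λ1)/y + k²(λ0² + λ1²))] − 1.96} = 92%, in line with the stated figure of over 80%.

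**2. If the vaccine were individually randomized in the subsets.**

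- Vi-TT clusters, children given MCV-A: 1,500 × 1/2 + 300 × 1/3 = 750 + 100 = 850.
- Control clusters, children given Vi-TT: 1,500 × 1/2 + 300 × 2/3 = 750 + 200 = 950.

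With crossover fractions f_V and f_C and rate ratio r, effectiveness analysed by cluster arm is

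1 − [(1 − f_V) r + f_V] / [1 − f_C (1 − r)].

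The planning rates give r = 0.0007/0.0036 = 0.194 (80.6%, rounded to 80% in the plan), so both values of r are shown. Coverage of 65% gives 0.65 × 11,500 = 7,475 vaccinees per arm.

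| Vaccinees per arm | f_V | f_C | Effectiveness, r = 0.20 | Effectiveness, r = 0.194 | Power at y = 165 (planning rates, diluted) |
|---|---|---|---|---|---|
| 11,500 | 7.4% | 8.3% | 72.3% | 72.8% | 81% |
| 7,475 | 11.4% | 12.7% | 67.6% | 68.1% | 73% |

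Example, first row, r = 0.20: (0.926 × 0.2 + 0.074)/(1 − 0.083 × 0.8) = 0.259/0.934 = 0.277, hence 72.3%.

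By subset, at 11,500 per arm and r = 0.20: safety alone gives 73.4%, immunogenicity alone 79.0%. Nearly all the dilution comes from the safety subset.

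**3. If the vaccine follows the cluster: safety bound.** Children per cluster m = 1,500/40 = 37.5; design effect = 1 + 36.5 × ICC. The article gives no ICC for adverse events. For a binary outcome, ICC = k²p/(1 − p). Borrowing k = 0.5 as an assumption, at p = 0.002:

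ICC = 0.25 × 0.002/0.998 = 0.0005; design effect 1.02; bound 0.2% × 1.02 = 0.204%.

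| ICC | Design effect | Bound | k implied at p = 0.2% |
|---|---|---|---|
| 0.0005 | 1.02 | 0.204% | 0.5 |
| 0.005 | 1.18 | 0.24% | 1.6 |
| 0.01 | 1.37 | 0.27% | 2.2 |
| 0.02 | 1.73 | 0.35% | 3.2 |

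**4. If the vaccine follows the cluster: immunogenicity.** After 25% drop-out an age stratum has 150 and 75 evaluable, or 150/40 = 3.75 and 75/40 = 1.9 per cluster. At ICC 0.01 and 0.02 the design effect is at most 1.03 and 1.06. Taking a one-sided 0.025 level (none is stated), non-inferiority power per stratum moves from 65.4% to 64.8% and 64.2%, and to 62.3% at ICC 0.05. These powers show only the change due to clustering. Without a stated level or target power they do not show that 600 is wrong.

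**The case against.** The strongest reply is that the operational text already settles the matter. Sections 2.2 and 2.4 put every enrolled participant on the cluster's vaccine, the latter in the very paragraph that covers the immunogenicity blood sample, and Section 2.4 speaks of participants being selected for the subset. The subset lists can then be read as lists for sampling. Section 2.6 never says that the 3,000 were individually randomized; it says only that they are enrolled 1:1 by arm. That description of the safety subset rests on one parenthesis in Section 2.3. This stands, and it makes vaccine-by-cluster the likely intent. It does not remove the contradiction: Section 2.3, and Section 2.6 for the immunogenicity strata, still state an allocation that the design cannot have.

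It can also be said that the 0.2% bound is sound. That largely stands. An ICC of 0.005–0.02 for an event at a 0.2% rate implies between-cluster variation of 1.6 to 3.2, against the 0.5 that the article assumes for typhoid. Finally, the method for subset intervals is commonly left to an analysis plan, which is not shown. Its absence here is therefore no fault.

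**Conclusion.** The contradiction is real and should be corrected. The article describes subset children as individually randomized to vaccine in a trial that assigns vaccine by cluster. The likely intent is individual selection with the vaccine following the cluster.

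Two stronger readings are tempting, and the documents do not support them. The first is that the primary comparison will be contaminated. Sections 2.2 and 2.4 say otherwise, so the fall to about 72–73% (about 68% at 65% coverage) measures what the wording would do if it were followed, under the sampling assumptions above. The second is that the subset precision is wrong. With the article's k of 0.5 borrowed for adverse events, the safety bound stays at about 0.20%; it reaches 0.24–0.35% only under an assumed ICC of 0.005–0.02. The loss for immunogenicity is small, about 1 point of power or less per stratum up to ICC 0.02 and about 3 points at 0.05.

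**What to change.** In Section 2.3 (both subsets) and in the immunogenicity sentence of Section 2.6, replace the individual-randomization wording with: *randomly selected, stratified by arm and age, from children vaccinated according to their cluster's allocation*. In Section 2.4, state that the subset lists govern selection only and never the vaccine given, and bring the 1:1 assignment wording for the safety subset into line.

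Treat the arm comparisons in both subsets as cluster-randomized, with intervals that allow for clustering. Note beside the 0.2% figure that it assumes independent participants; it need not be recalculated.

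The cost is a few words of text and a routine cluster adjustment in the subset analyses. No sample size changes.
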